### 2.6. tDCS Treatment, Simulation and Blinding

#### 2.6.1. tDCS Device

Participants will undergo an intervention tDCS treatment using a battery-driven and portable device (Neurophet innk, Neurophet, Seoul, Republic of Korea), programmed to deliver either active or sham tDCS. The device delivers 2.0 mA (with 30 s for ramping up and ramping down; Figure 2) of the direct current through the two sponge-coated electrodes (electrode size: 5 × 5 cm^2^). The tDCS device used in this study can check the impedance values occurring in patient’s skin, in real time, during all tDCS sessions. If an impedance above 13 kOhm occurs, the stimulation is stopped, and the medical device investigator confirms the patient’s condition and skin. This may reduce the adverse events that may occur on the patient’s skin, due to the increased impedance. In the sham-tDCS condition, the device delivers 120 s of the current, including 30 s for ramping at the beginning and end of each session, to maintain the blinding procedure. The tDCS treatment was performed 10 times over a total of 2 weeks, and sham-tDCS was also applied 10 times with sham stimulation for 2 weeks. Following this duration, both opt-tDCS and con-tDCS groups, but not the sham-tDCS group, will receive the opportunity to provide additional written consent for an extension study; if the participants give consent, the extension study will be conducted for two additional weeks. During the 2 or 4 weeks of intervention, if there was a usual rehabilitation program that was being performed before participation in this study, the program and frequency could be continued without any changes. The detailed intervention methods regarding tDCS for each group, is as follows (Figure 3a). The representative figure which represents the difference between optimized tDCS and conventional tDCS simulation results in participant is Figure 3b.

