### 2.9. Secondary Outcomes

The secondary outcomes include the changes in the motor evoked potentials (MEPs); frequency power and coherence of electroencephalography (EEG); upper extremity functions; Wolf motor function test (WMFT) [29,30], box and block test (BBT) [31], performance in activities of daily living (ADLs) [32], and adverse events with the 1-month follow-up assessment (for details, see Table 1).

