### 2.11. Statistical Analyses

The descriptive statistics (average, standard deviation, median, minimum, and maximum) are presented for each group for the change in the primary outcomes at 2 weeks, compared to the baseline (0 weeks), and the comparison of differences between the groups will be the repeated measures ANCOVA that considers time as a covariate. If statistically significant changes were confirmed in the comparison of the differences between the three groups, a repeated ANCOVA that considered the timing of the differences between the two groups (e.g., opt-tDCS and con-tDCS, opt-tDCS and sham-tDCS) was planned as a post hoc analysis. The results corresponding to the secondary outcomes will be presented as descriptive statistics (frequency, ratio) for each group, based on the change in score at 4 weeks, and the difference between the two groups, will be analyzed using the repeated measures ANCOVA, that considers time.

The primary outcome will be analyzed in the intention-to-treat population, and the safety outcomes will be analyzed in the per-protocol population. No protocol interim analysis is planned, and a total of 42 patients will be enrolled in this clinical trial over a total of 30 months. This sample will be able to evaluate the clinical applicability of the optimized tDCS treatment in the subacute to chronic stages of a stroke and aims to verify the trends in the intergroup differences and the changes to demonstrate the statistically significant differences in the upper limb function improvement between the two groups.

The outcome analysis of this trial will be largely divided into a safety set (SS) group, a full analysis set (FAS) group, and a per-protocol set (PP) group. The efficacy evaluation will analyze the PP group as the main analysis group and analyze the FAS group. If the results are different across the analysis groups, the results of each analysis method will be presented and analyzed to identify the reason. The safety assessment will be carried out in the SS group, and the significance level will be set at 0.05.

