### 2.12. Safety, Protocol, and Data Monitoring

The potential tDCS adverse events and side effects that may occur to the participants during the treatments are identified during stimulation as well as up to 30 min after the end of stimulation. If adverse events occur, they will be diagnosed by a study physician and will be reported to IRBs, according to the criteria of severity (mild, moderate, and severe). If the events are severe, the investigators must report that to the Korean Ministry of Food and Drug Safety, which will advise whether to continue, modify or stop the intervention and decide whether to unmask the group assignment.

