**Figure 3 brainsci-12-01673-f003:**
[figure not shown]

[figure not shown]
(**a**) The intervention methods for the three groups. (**b**) Computational results of the optimized and conventional tDCS simulation.

**Table 1 brainsci-12-01673-t001:** Schedule of enrollment, interventions and assessment.

	Screening	Intervention			Outcomes	Extended Intervention		Outcomes
		Baseline						
Visit	V1	V2	V3~V6	V7~V11	V12	V13~V17	V18~V22	V23
ENROLLMENT								
Informed consent	V					V		
Eligibility screen	V	V						
Randomized allocation		V						
INTERVENTIONS								
Opt-tDCS Conv-tDCS Sham-tDCS		V	V	V		V	V	
ASSESSMENTS								
Baseline variables Vital signs Physical examination MRI scan MEPs EEG Functional examinations		V						
Outcome variables MRI scan MEPs EEG Functional examinations		V			V			V
Other variables Adverse events		V	V	V	V	V	V	V

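### The safety assessment is not limited to the ten sessions common to all arms, so the extension, open only to the active arms, could inflate adverse events relative to sham

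*Protocol article*

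**What the plan says.** All references are to the protocol article.

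- **Randomised phase (Section 2.6.1).** All arms have the same number of sessions: "The tDCS treatment was performed 10 times over a total of 2 weeks, and sham-tDCS was also applied 10 times".
- **Extension (Section 2.6.1).** Afterwards "both opt-tDCS and con-tDCS groups, but not the sham-tDCS group, will receive the opportunity to provide additional written consent for an extension study". It is voluntary: "if the participants give consent, the extension study will be conducted for two additional weeks". No uptake is stated.
- **Collection (Table 1).** The row "Other variables Adverse events" is marked at V2, V3–V6, V7–V11, V12, V13–V17, V18–V22 and V23, so it runs through the extension.
- **Detection (Section 2.12).** Adverse events "are identified during stimulation as well as up to 30 min after the end of stimulation".
- **Role (Section 2.9).** The secondary outcomes include "adverse events with the 1-month follow-up assessment".
- **Analysis (Section 2.11).** Secondary outcomes are summarised by group, as frequencies and ratios, on score change at four weeks. On safety, "The safety assessment will be carried out in the SS group", with a significance level of 0.05. No period, cut-off at V12 or allowance for exposure is given. Earlier in the same section, safety outcomes are assigned to the per-protocol population instead.

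**The concern.** The randomised comparison with sham is balanced for exposure only up to V12. After that, patients in the active arms can have more stimulation sessions, and more observed sessions in which an event can be recorded, while sham patients cannot. Section 2.11 fixes the primary outcome at two weeks, before the extension, but sets no such limit for safety. The only reporting time it gives for secondary outcomes is four weeks, which for a patient who extends is the end of the extension.

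At stake is the safety statement about personalised tDCS, which the abstract names among the trial's contributions and for which sham is the natural reference. If extension events enter a by-arm table, an apparent excess in the active arms could reflect extra sessions and not extra risk per session. A purely descriptive table would mislead in the same way as a test.

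**Working it through.** **Step 1. Reproduce the session count.** From Table 1, V2 (1) + V3–V6 (4) + V7–V11 (5) = 10, which matches the 10 sessions in Section 2.6.1. The extension is V13–V17 (5) + V18–V22 (5) = 10. An active patient who extends therefore has 20 sessions and a sham patient 10.

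**Step 2. Inputs.** From the document: 42 patients allocated 1:1:1, so 14 per arm and 28 active against 14 sham; significance level 0.05. Not in the document, and so assumed:
- per-session event probability q, the same in every arm, from 1% to 10%
- extension uptake u among active patients, at 0, 50% and 100%
- independent sessions, and uptake unrelated to a patient's risk
- a two-sided Fisher exact test, as illustration only, since no safety test is named

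**Step 3. Event counts.** Expected events per patient are 10q in sham and 10q(1 + u) in an active arm, a ratio of 1 + u whatever q is. This gives 1.0 at no uptake, 1.5 at 50% and 2.0 at 100%. For example, at q = 5% the 14 sham patients would have 14 × 10 × 0.05 = 7 events. The 28 active patients would have 14 at no uptake, 21 at 50% and 28 at 100%.

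**Step 4. Patients with at least one event.** For sham, P = 1 − (1 − q)^10. For active, P = u[1 − (1 − q)^20] + (1 − u)[1 − (1 − q)^10]. At q = 5%: 1 − 0.95^10 = 40.1%, 1 − 0.95^20 = 64.2%, and at u = 50% the mean of the two is 52.1%.

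| q | Sham | Active, u = 50% | Excess (points) | Active, u = 100% | Excess (points) |
|---|---|---|---|---|---|
| 1% | 9.6% | 13.9% | 4.3 | 18.2% | 8.6 |
| 2% | 18.3% | 25.8% | 7.5 | 33.2% | 14.9 |
| 5% | 40.1% | 52.1% | 12.0 | 64.2% | 24.0 |
| 10% | 65.1% | 76.5% | 11.4 | 87.8% | 22.7 |

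**Step 5. Illustrative false-positive rate.** Fisher exact test, all outcomes enumerated, with no true per-session difference:

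| q | 28 v 14, equal exposure | 28 v 14, u = 50% | 28 v 14, u = 100% | 14 v 14, u = 100% |
|---|---|---|---|---|
| 1% | 1.9% | 1.5% | 3.5% | 2.6% |
| 2% | 2.8% | 4.9% | 13.3% | 7.5% |
| 5% | 3.8% | 9.3% | 27.2% | 13.0% |
| 10% | 3.7% | 8.6% | 34.8% | 17.2% |

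**Step 6. After a cut-off at V12.** Planned exposure is 10 sessions in every arm, the event ratio is 1.0, and the 28 v 14 test stays at the equal-exposure values, all below 5%.

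**The case against.** A reader might infer that the plan does count events over 20 active sessions against 10 sham sessions, and so builds a false excess into the safety result. The document does not support that. Section 2.11 names a safety population and a significance level. It prescribes no between-arm test of adverse events, no pooling of the two periods, and no merging of the active arms against sham. Section 2.6.1 calls the second period an extension study with its own consent, and Table 1 sets it apart from the main intervention, which points towards separate reporting. The four-week sentence speaks of score changes analysed by repeated measures ANCOVA, which does not describe event counts. A journal article may also leave reporting periods to the full protocol or analysis plan.

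Much of this stands, and it makes the point conditional. It does not remove it. The article lists adverse events as a secondary outcome, collects them through V23, gives four weeks as the reporting time for secondary outcomes, and fixes an exposure difference by design. A by-arm summary to V23 would be consistent with that text.

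Four further limits stand:
- The largest rejection rates need full uptake and a 28 v 14 test that the plan does not name.
- If events cluster in susceptible patients, doubling the sessions adds fewer new patients with events than Step 4 shows.
- Detection is not confined to sessions, because V12 and V23 also record events and Section 2.9 mentions a one-month follow-up.
- A fix that only discarded later events would lose follow-up events in sham patients.

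**Conclusion.** The point holds in conditional form. Exposure to stimulation and to event detection can differ between active and sham after V12, and Section 2.11 does not confine the safety assessment to the common period. If events to V23 are summarised by arm, counts per active patient are inflated by 1 + uptake relative to sham. At 50% uptake and per-session risks of 2%, 5% and 10%, the false excess of patients with an event is 7.5, 12.0 and 11.4 percentage points. The illustrative 28 v 14 test then rejects in about 5%, 9% and 9% of trials, or 13%, 27% and 35% at full uptake, against 3–4% with equal exposure. At a risk of 1% per session the test hardly moves, although the count ratio is unchanged.

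These figures rest on assumed risks and uptake and on independent sessions. With no uptake there is no bias. Opt-tDCS and con-tDCS have equal planned access to the extension, so their comparison with each other is unequal only if uptake differs. It would go too far to say that the trial's safety result will be biased.

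**What to change.** In Section 2.11 or the analysis plan:

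1. Make the comparison with sham on adverse events from V2 to V12, in the safety set.
2. Report events after V12 separately by arm, with no test against sham. For extension participants give them per session delivered, and include any follow-up events in sham patients and in active patients who do not extend.
3. Reconcile the two safety populations named in Section 2.11 (per-protocol and safety set).

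Also check the intervention row of Table 1. As extracted, one row names "Opt-tDCS Conv-tDCS Sham-tDCS" and is marked through V13–V22, while Section 2.6.1 excludes sham from the extension. This may only be an effect of table extraction. If it is printed that way, the two places must be reconciled.

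The cost is one or two sentences for items 1 and 2, with no new data. The downside is that extension and late events no longer enter the comparison with sham. They are still reported.

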### 2.12. Safety, Protocol, and Data Monitoring

The potential tDCS adverse events and side effects that may occur to the participants during the treatments are identified during stimulation as well as up to 30 min after the end of stimulation. If adverse events occur, they will be diagnosed by a study physician and will be reported to IRBs, according to the criteria of severity (mild, moderate, and severe). If the events are severe, the investigators must report that to the Korean Ministry of Food and Drug Safety, which will advise whether to continue, modify or stop the intervention and decide whether to unmask the group assignment.

## 3. Discussion

This prospective multicenter double-blind controlled trial aims to prove that the patient’s own MRI-based optimized tDCS treatment beneficially impacts the improvements in the upper limb function and the parameters related to ADLs or neurophysiology in patients with a stroke. Although positive results for the tDCS effectiveness has been reported by several studies, the level of clinical evidence and practical use in the clinical settings are still limited [24,25]. Several studies evaluating the tDCS effectiveness have shown inconsistent results for improving the upper limb function in patients with a stroke [14,33,34], and the reasons inferred by researchers for the limited effectiveness are as follows: (1) there is a variety in the tDCS stimulation montage and parameters used; and (2) the personalized optimization of tDCS has not been applied. Therefore, recent studies have sought ways to overcome individual variation in the tDCS treatment effects.

This challenge contributes to previous studies performing randomized controlled trials with a large sample size; in addition, these studies have suggested to conduct dose-controlled tDCS studies with MR images, based on head models [35]. A previous study created computational models with MR images of two chronic stroke patients, analyzed the distribution of the TMS and tDCS-induced electrical fields, and tried to verify that transcranial brain stimulation is a safe method for chronic stroke patients, compared to healthy adults [36]. This report described a computational study on how the location of the lesion and brain atrophy could affect the stimulation-induced electrical fields and effects and intended to provide a basis for the computational studies to use MR image-based head models for clinical application. However, the fact that only two patients were analyzed and the relative positions of the tDCS electrode and TMS coil, compared to the lesion location, were divided into only nine positions, limited this study as a basis for application in clinical patient cases. Another study used the necessary research tools to segment the brain lesions using individual images more accurately and to simulate tDCS in a manner that considered the lesions and reviewed the clinical applicability. In this study, the results were compared and analyzed across each of the 16 conductivity values and considered that the tDCS-induced electrical fields depended on the conductivity of each region of the brain tissue [37].

In this way, previous studies have attempted the strategy of reducing the variations, using individual MRI-based computational models, but they could not actively achieve adequate results because it is not easy to apply procedures including MR image analysis and segmentation, volume conductive head modeling, and stimulation simulation. In particular, the description of the image analysis and segmentation is not yet perfect, and researchers must use several research tools for performing a series of procedures, including MR image segmentation, 3D brain modeling, and stimulation simulation [38]. Such open-source research tools are generally difficult to use, require a long period of time, and above all, they are not easy to apply in clinical fields, due to poor user convenience. Taking this into account, we developed a personally optimized tDCS model with a MRI-based phantom head [25] and developed the software ‘tES LAB’, which can calculate the tDCS-induced electrical fields. tES LAB is GUI-based and has the advantage of being able to perform a series of processes, including MR image segmentation and personally optimized tDCS simulations, within one software package, so it can be used without professional researcher personnel.

However, our study protocol has several limitations. First, the patients in a craniectomy state would be excluded from this study because of unsolved safety issues. Usually, patients with a huge intracranial hemorrhage may be taken for a craniectomy. The distributions of patients slightly differ from the real-world distribution. Second, we conducted tDCS with just 2.0 mA in this study protocol. Recently, 4.0 mA tDCS may stimulate more widely, compared to 2.0 mA [39]. However, the Korea Disease Control and Prevention Agency permitted up to 2 mA for tDCS in the clinical field. Thus, we planned to conduct tDCS with 2 mA in this protocol.

In this study, we will attempt to apply the optimized tDCS treatment that considers the brain structure of individual patients and try to improve treatment in real clinical environments, involving rehabilitation in subacute to chronic periods, compared with a conventional tDCS, which is the most active period of rehabilitation after stroke. If stroke patients, during this period with motor disabilities, can safely undergo tDCS treatment together with parallel treatment regimens, acute or chronic stroke patients after discharge may also be able to use it. Our findings are expected to show that the patient’s optimized tDCS treatment will probably be pragmatic for patient care and contribute to overcoming previously reported limitations on tDCS treatment. In addition, it is expected that the effect of optimized tDCS, which has always been limited only to simulation study results, can be verified from the actual therapeutic point of view.

Trial Status: Recruitment of participants started in November 2011 and will be completed in December 2023. This manuscript reports protocol version 4.1 (25 January 2022).

## Figures and Tables

**Figure 1 brainsci-12-01673-f001:**
[figure not shown]
Study design.

**Figure 2 brainsci-12-01673-f002:**
[figure not shown]
tDCS and sham tDCS protocol.

**Figure 3 brainsci-12-01673-f003:**
[figure not shown]

[figure not shown]
(**a**) The intervention methods for the three groups. (**b**) Computational results of the optimized and conventional tDCS simulation.

**Table 1 brainsci-12-01673-t001:** Schedule of enrollment, interventions and assessment.

	Screening	Intervention			Outcomes	Extended Intervention		Outcomes
		Baseline						
Visit	V1	V2	V3~V6	V7~V11	V12	V13~V17	V18~V22	V23
ENROLLMENT								
Informed consent	V					V		
Eligibility screen	V	V						
Randomized allocation		V						
INTERVENTIONS								
Opt-tDCS Conv-tDCS Sham-tDCS		V	V	V		V	V	
ASSESSMENTS								
Baseline variables Vital signs Physical examination MRI scan MEPs EEG Functional examinations		V						
Outcome variables MRI scan MEPs EEG Functional examinations		V			V			V
Other variables Adverse events		V	V	V	V	V	V	V

## Data Availability

The data will be presented in this study via the next article after the completion of the double-blind randomized controlled trial.
